### Sample size

To demonstrate the presence of an effect on the PAM between t0 and t2 of at least 0.5 standard deviations as statistically significant in a one-tailed test at alpha = 0.05 and a power of (1 - beta) = 0.80, at least 51 participants in each condition will be required at three months follow-up. Anticipating a dropout rate of 25% between t0 and t2 (based on earlier research in this population [38]), 68 participants per condition arm need to be included at baseline (t0). In total, 136 cancer patients will be recruited for this study.

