### Statistical analyses

All analyses will be conducted according to the intention-to-treat principle. Descriptive statistics will be generated to describe all sociodemographic and clinical characteristics, and outcome measures. To analyze whether randomization resulted in a balanced distribution of patient characteristics across the study arms, chi-square tests and independent samples t-tests will be used. When data is not normally distributed, Mann-Whitney U tests will be performed. In addition, independent samples t-tests will be used to test whether there are differences in outcome measures across study arms at baseline.

Linear Mixed Models (LMM) will be used to determine the efficacy of Oncokompas (e.g. changes in patient activation in the intervention group and the control group between t0, t1, and t2) by comparing longitudinal changes between both groups with fixed effects for study arm, time, and their two-way interaction, as well as a random intercept for subjects, and, if necessary, for referring hospitals. In case of baseline differences between study arms in sociodemographic and clinical characteristics, or outcome measures, the LMM analyses will be corrected for these differences. LMM will also be used to determine whether age, gender, socio-economic status (e.g. education level and work situation), cancer type, treatment modality, time since treatment, and baseline quality of life moderate the efficacy of Oncokompas. Fixed effects will be used for study arm, time, the potential moderator, and all two-way and three-way interaction effects, as well as a random intercept for subjects, and, if necessary, for referring hospitals.

Post-hoc analyses will be applied when significant results are found in the efficacy and moderation analyses mentioned above. Independent samples t-tests with Bonferroni correction will be used to measure the differences between the intervention group and the control group at follow-up measurements. To measure the effect sizes (ES) of the intervention, the (between group) Cohen’s d will be calculated. The magnitude of the ES is classified as large (≥ 0.80), moderate (0.50–0.79) or small (< 0.50) [39].

IBM Statistical Package for the Social Sciences (SPSS) version 26 (IBM Corp., Armonk, NY USA) will be used to perform all statistical analyses. All tests will be one-tailed. A *p*-value < 0.05 will be considered significant for all analyses.

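### The post-hoc t-tests measure the follow-up arm differences without baseline and only on patients observed at that visit, so they can report a different quantity from the one the mixed model tested

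*Protocol article*

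**What the plan says.** All of this is in the protocol article.

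- **Principle** (Statistical analyses): "All analyses will be conducted according to the intention-to-treat principle".
- **Efficacy test** (Statistical analyses): "Linear Mixed Models (LMM) will be used to determine the efficacy of Oncokompas", and it does so "by comparing longitudinal changes between both groups with fixed effects for study arm, time, and their two-way interaction". A random subject intercept is included, so baseline is one of the modelled measurements.
- **Baseline differences** (Statistical analyses): if the arms differ at baseline, "the LMM analyses will be corrected for these differences". No such correction is named for any other analysis.
- **Follow-up step** (Statistical analyses): "Post-hoc analyses will be applied when significant results are found in the efficacy and moderation analyses mentioned above". The method is then fixed: "Independent samples t-tests with Bonferroni correction will be used to measure the differences between the intervention group and the control group at follow-up measurements".
- **Effect size** (Statistical analyses): "To measure the effect sizes (ES) of the intervention, the (between group) Cohen’s d will be calculated". The text does not say whether the means and SD are raw or model-based.
- **Expected loss** (Sample size): "Anticipating a dropout rate of 25% between t0 and t2", from 68 to 51 per arm.
- **Missing data** (Economic outcomes): multiple imputation is named for the cost questionnaires and EQ-5D utilities, and for nothing else.

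**The concern.** The LMM compares change from baseline between arms and keeps patients who have a baseline or t1 value but no t2 value. The t-test compares raw follow-up means among those who answered that questionnaire. These are two different estimators. They part company when the arms differ by chance at baseline, and when the patients lost from one arm are unlike those lost from the other.

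The second case is plausible here: the patients have incurable cancer, and only one arm is given an application to work with during the three months. A reader could then see a significant model result beside an arm difference of another size. If Cohen's d follows the t-test, the effect size classed as small, moderate or large would carry the same distortion.

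This is a stated choice of method, not a detail left open for an analysis plan.

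**Working it through.** **1. The plan's own figures.** Effect 0.5 SD, one-tailed alpha 0.05, power 0.80. The exact two-sample t-test solution is 50.15, so 51 per arm. Allowing for dropout, 51 / 0.75 = 68 per arm, 136 in total. The stated sample size reproduces, and it is that of an unadjusted comparison of 51 v 51.

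**2. Who enters the t2 t-test.** 0.25 x 68 = 17 per arm have no t2 value. The test uses 51 v 51, or 102 of 136.

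**3. Bias of the raw t2 difference.** The documents give neither a PAM correlation nor a dropout mechanism, so both are assumed. Scores have SD 1, the true t2 difference is 0.50, and the correlation rho between any two visits is 0.3, 0.5 or 0.7. The log-odds of dropout are log(0.25/0.75) minus s times the baseline score. With s = 0, 25% drop out; with s = 1, low-baseline patients leave more often and about 29% drop out.

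By numerical integration, with s = 1 the mean baseline score of those retained is +0.24 SD. If s = 1 in the intervention arm and s = 0 in the control arm, the expected raw t2 difference is 0.50 + rho x 0.24:

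| rho | Expected raw difference | Simulated raw difference | Simulated LMM change contrast |
|---|---|---|---|
| 0.3 | 0.50 + 0.07 = 0.57 | 0.56 to 0.57 | 0.50 |
| 0.5 | 0.50 + 0.12 = 0.62 | 0.61 to 0.62 | 0.50 |
| 0.7 | 0.50 + 0.17 = 0.67 | 0.67 to 0.68 | 0.50 |

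The simulations used 68 per arm; ranges are across repeated runs, and one run put the LMM contrast at 0.49 to 0.50.

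With s = 0 in both arms, or s = 1 in both arms, the simulated raw difference is 0.50 to 0.51. The shift of 0.24 rho then cancels or is absent.

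**4. Precision.** With complete data, the variance of the planned arm-by-time contrast relative to the raw t2 difference is 2(1 - rho): 1.40, 1.00 and 0.60 at rho 0.3, 0.5 and 0.7. With 17 per arm missing at t2, generalised least squares gives ratios to the 51 v 51 t-test of 1.27, 0.92 and 0.56. The planned contrast is therefore less precise than the t-test at 0.3, about equal at 0.5 and more precise at 0.7.

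The familiar factor 1/(1 - rho^2), which is 1.33 at rho 0.5, belongs to a model that adjusts for baseline. The planned LMM does not have that form.

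**5. Power, like for like.** Noncentral t, 51 per arm, effect 0.5 SD, rho 0.5, residual SD sqrt(1 - 0.25) = 0.866 with adjustment:

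| One-sided alpha | Unadjusted t-test | With baseline adjustment |
|---|---|---|
| 0.05 | 0.81 | 0.89 |
| 0.025 | 0.71 | 0.82 |

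The 0.025 row applies if the Bonferroni correction covers the two follow-up visits. The article does not state the family, so that is an assumption.

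**The case against.** The strongest reply is that the t-tests decide nothing. Efficacy is determined by the LMM, and the t-tests are a post-hoc description run only after a significant result. That stands, and it limits the point to how the effect is measured and reported.

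Three stronger readings are tempting, and the document does not support them.

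- **That the t-tests contradict intention-to-treat.** They compare patients by allocated arm, and nothing excludes anyone for not using the application. Analysing available data weakens a full intention-to-treat analysis but does not flatly contradict the principle.
- **That Cohen's d is a raw estimate on completers.** The sentence on d follows the t-tests and names no other source, so this is the natural inference, but the source of the means is not stated.
- **That any dropout related to baseline biases the raw difference.** It does not: step 3 shows no bias when the same baseline-related dropout acts in both arms. The article anticipates a single 25% and gives no reason to expect different rates.

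A reader might also expect the model-based contrast to be more precise in every case. Step 4 shows otherwise. Nor should power of 0.71 be set against 0.89 as the price of ignoring baseline, because that comparison changes the alpha level as well.

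What remains after these concessions is that the named method has no baseline term, uses only those observed, and departs from a model that already supplies the wanted contrast.

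**Conclusion.** The point holds as a recommended change to the reported estimate. It is not a threat to the efficacy test or the sample size.

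The size depends on assumptions. Under dropout that depends on baseline in the intervention arm only, the raw t2 difference overstates a 0.50 SD effect by about 0.06 to 0.18 SD over correlations of 0.3 to 0.7, and the LMM contrast does not. Under dropout that acts alike in both arms, the bias is nil. The LMM's advantage rests on dropout being explained by the scores already observed; if it depends on unobserved scores, neither method is protected.

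Two defects need no assumption about dropout: the reported difference need not be the quantity tested, and a baseline correction judged necessary in the LMM disappears from the t-tests.

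**What to change.** Replace the post-hoc t-tests with the arm contrasts in change from baseline to t1 and to t2, taken from the planned LMM with confidence intervals. State that Cohen's d is computed from those contrasts, and name the SD used as the divisor.

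The cost is a change of wording and a contrast statement in a model that will be fitted anyway. In return, the reported difference is the one tested, it uses all available data, and it keeps any baseline correction.

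Do not justify the change by a gain in precision unless the model itself is altered to adjust for baseline, for example with baseline as a covariate or a common baseline mean for both arms. That is a separate choice. At correlation 0.5 it would bring the gain shown in step 5.

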### Outcome assessment

The primary outcome measure to assess the efficacy of Oncokompas is patient activation. Secondary outcome measures are general self-efficacy and health-related quality of life. Also cost-utility outcomes will be evaluated. Outcome measures will be collected through online questionnaires at baseline (t0), two weeks after randomization (t1), and three months after the baseline measurement (t2).

An overview of the primary and secondary outcome measures is shown in Table 2.

**Table 2 Tab2:** Measurement overview

Aim	Outcome measures	Time point		
	*Instrument*	Baseline (t0)	Two weeks after randomization (t1)	Three months after baseline measurement (t2)
Efficacy				
*Primary outcome measure*	Patient Activation	X	X	X
	*Patient Activation Measure (PAM)*			
*Secondary outcome measures*	Self-efficacy	X	X	X
	*General Self-Efficacy Scale (GSE)*			
	Health-related quality of life	X	X	X
	*EORTC QLQ-C15 PAL*			
Cost-utility				
	Quality-adjusted life years	X		X
	*EuroQol 5 Dimensions (EQ-5D)*			
	Medical costs	X		X
	*iMTA Medical Consumption* * Questionnaire (iMCQ)*			
	Productivity costs	X		X
	*iMTA Productivity Cost Questionnaire (iPCQ)*			

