#### Quality of life

Quality of life is measured by the European Organization for Research and Treatment of Cancer Quality of Life Questionnaire for cancer patients in palliative care (EORTC QLQ-C15-PAL). The EORTC QLQ-C15-PAL is an abbreviated 15-item version of the EORTC QLQ-C30 questionnaire. The EORTC QLQ-C15-PAL questionnaire is specifically designed for patients with advanced, incurable and symptomatic cancer with a median life expectancy of a few months [33].

The EORTC QLQ-C15-PAL comprises a global quality of life scale, two functional scales (physical and emotional functioning), two symptom scales (fatigue and pain), and four single items (dyspnea, insomnia, appetite loss, and constipation) [33]. All scales range in score from 0 to 100. A high score on the global quality of life scale represents a high quality of life and a high score on a functional scale represents a high or healthy level of functioning. A high score on a symptom scale indicates a high level of symptoms [34].

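### The only stated follow-up of a significant moderator is an arm-versus-arm t-test, which fits numerical moderators badly and leaves the fitted mixed model.

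*Protocol article*

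**What the plan says.** The Statistical analyses section of the protocol article sets out three steps.

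1. **Moderation model.** The candidate moderators open with "LMM will also be used to determine whether age, gender" and socio-economic status, continue with cancer type and treatment modality, and close with "time since treatment, and baseline quality of life moderate the efficacy of Oncokompas". For the model, "Fixed effects will be used for study arm, time, the potential moderator, and all two-way and three-way interaction effects". There is also a random intercept per patient and, if needed, per referring hospital.
2. **Trigger.** "Post-hoc analyses will be applied when significant results are found in the efficacy and moderation analyses mentioned above".
3. **Follow-up method.** "Independent samples t-tests with Bonferroni correction will be used to measure the differences between the intervention group and the control group at follow-up measurements". A between-group Cohen's d accompanies it.

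No other probe of a moderation result is named. The article does not say whether the numerical moderators enter the model as continuous or grouped, and it gives no cut-points. It does not state how many tests the Bonferroni correction covers. For the quality-of-life instrument, the Quality of life section says "All scales range in score from 0 to 100", so that moderator is a score and not a category.

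**The concern.** A t-test of intervention against control compares two means. Run on all patients, it does not contain the moderator and so cannot follow up a moderation result. To bring the moderator in, patients must be grouped. That is natural for gender, education, work situation, cancer type and treatment modality. It is not natural for age, time since treatment or a 0 to 100 quality-of-life score.

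The t-test also differs from the model whose result it is meant to explain:

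- The model compares longitudinal changes; the t-test compares levels at follow-up and drops each patient's baseline value.
- The article promises that the mixed models will be corrected for baseline differences between arms; the t-test carries no such correction.
- The model uses the t0 and t1 data of patients lost before t2; a t-test at t2 does not.

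At stake is any statement about which patients benefit from Oncokompas. It would rest on a weaker analysis than the one already fitted, and the two could disagree.

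**Working it through.** **Inputs from the article.** Sample size section: effect 0.5 SD, one-tailed alpha 0.05, power 0.80, 51 per arm at t2, 25% dropout, 68 per arm at baseline. Outcome assessment: two follow-ups, t1 and t2.

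**Assumptions not in the article.** The split is at the median and fixed in advance. The 0.5 SD applies to the outcome compared by the t-test. The Bonferroni family is 2 tests (two halves at one follow-up) or 4 tests (two halves at two follow-ups).

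**Step 1: the plan's own figure.** A one-sided two-sample t-test for 0.5 SD at alpha 0.05 and power 0.80 needs 50.15 per arm, rounded up to 51. Then 51 / (1 − 0.25) = 68 per arm, and 2 × 68 = 136. The stated sample size reproduces.

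**Step 2: size of a half.** 51 / 2 = 25.5, so about 25 per arm in each half at t2.

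**Step 3: power within a half.** The noncentrality is d × √(n/2) = 0.5 × √(25/2) = 1.768, with 2 × 25 − 2 = 48 degrees of freedom.

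| Tests in Bonferroni family | One-tailed alpha | Critical t | Power for 0.5 SD | Effect detectable with 80% power |
|---|---|---|---|---|
| 1 (no correction) | 0.05 | 1.677 | 54% | 0.71 SD |
| 2 | 0.025 | 2.011 | 41% | 0.81 SD |
| 4 | 0.0125 | 2.314 | 30% | 0.90 SD |

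With 26 per arm, the last two powers are 42% and 31%.

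**Step 4: data left out.** At the planned dropout, 68 − 51 = 17 patients per arm have a baseline value, and possibly a t1 value, but no t2 value. The mixed model uses those records; a t2 t-test does not.

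**Step 5: false positives, with and without the trigger.** This is a simulation under no effect anywhere: 51 per arm, normal moderator and outcome, one follow-up, one-tailed t-tests at 0.025 in each of two groups.

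| Procedure | t-tests always run | t-tests run only after a significant interaction (two-sided 0.05) |
|---|---|---|
| Fixed median split | about 5% | about 1% |
| Most favourable of seven cuts (20th to 80th percentile) | about 14% | 2 to 3% |

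The right-hand column is the one that matches the article, because the t-tests follow only a significant result. If the interaction counts as significant with 0.05 in either tail (10.1% of null runs), the rates are 0.194 × 0.101 = 2.0% and 0.397 × 0.101 = 4.0%. All rates are per moderator.

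**The case against.** The strongest reply is that this is detail a condensed article leaves to a fuller document. The moderators may enter the model already grouped, or a plan not shown may fix the cut-points. In either case the groups exist before any interaction is seen, and t-tests within groups follow directly. Missing cut-points alone are therefore no finding.

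That part stands. A reader might infer that a cut-point will be picked once a significant interaction is known, and might attach the 14% false-positive rate to it. The article supports neither step. It mentions no search for a cut, and its trigger brings the illustrative rate down to a few per cent per moderator.

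A reader might also argue that splitting at the median wastes much of the information on a linear moderator. That does not apply to the moderation test itself. If the moderator is kept continuous in the mixed model, the interaction test loses nothing, and the t-test only describes the result afterwards.

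For the categorical moderators, comparing arms by level is an ordinary follow-up, and the problem of splitting does not arise.

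What the reply does not remove is the stated method. Fixed cut-points would settle the grouping. They would not restore the power lost in halves, the change scores, the baseline correction or the partial data of patients who drop out.

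**Conclusion.** The point holds as a poor choice of method, not as a missing detail. The named probe of a significant moderator does not suit age, time since treatment or baseline quality of life, and it departs from the model that produced the finding.

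The size is a power of about 41% or 30% for 0.5 SD within a half-sample, against the 80% planned for the whole trial. This rests on a pre-set median split and on a Bonferroni family of 2 or 4 tests, neither of which the article states. Inflated false positives from a cut-point chosen after seeing the data are only a possibility, and no rate should be charged to the plan for it.

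Severity is minor. The follow-up is conditional and concerns secondary analyses. The primary mixed-model comparison, the moderation tests themselves and the 136 patients are unaffected.

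**What to change.** For moderation, replace the t-tests by contrasts from the three-way mixed model already planned. Report the arm difference in change from baseline to t1 and to t2, each with a 95% confidence interval:

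- for numerical moderators, kept continuous, at values stated in advance, for example the 25th, 50th and 75th percentiles of the baseline distribution;
- for categorical moderators, by level.

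If groups are preferred for presentation, state the cut-points before the data are analysed and still take the estimates from the model.

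The cost is a change of analysis wording. No patients, visits or data are added, and no new model is needed. The downside is that the contrasts assume that the effect varies linearly with a numerical moderator, and this should be said when they are reported. They use all patients rather than half, but the trial was not sized for moderation, so the intervals should be expected to be wide.

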### Economic outcomes

The cost-utility analysis will be conducted in agreement with the intention-to-treat principle. The incremental cost-utility ratio (ICUR) will be calculated by dividing the differences in total costs (i.e. mean costs in the intervention group minus mean costs in the control group) by the differences in QALYs (i.e. mean QALYs in the intervention group minus mean QALYs in the control group). To calculate total costs from a societal perspective, intervention costs, costs of healthcare (i.e. costs of healthcare use and medication), costs for patients and their families (e.g. travelling costs and help received from family and friends), and costs within other sectors (e.g. productivity losses from paid work) will be included. Also total costs from a healthcare perspective will be calculated, which includes intervention costs and the costs of healthcare.

By multiplying resource use by integral cost prices as presented in the Dutch Health Care Insurance Board (CVZ) guidelines on cost studies, costs of healthcare and costs for patients and their families will be calculated [40]. The friction cost method will be used to calculate costs within other sectors [41, 42].

The time horizon will be set at three months follow-up, and therefore neither costs nor effects will be discounted. QALYs will be calculated by multiplying the EQ-5D utility score by the appropriate time period it accounts for. When data are missing on the costs of healthcare, the costs for patients and their families and the costs within other sectors, measured with the iMCQ and iPCQ cost questionnaires, these will be imputed using multiple imputation. This also accounts for missing data on the utilities measured with the EQ-5D.

Non-parametric bootstrapping with 5000 imputations will be used to obtain 95% confidence intervals around the cost and QALY differences. A cost-utility plane will be plotted for the projection of the resulting pairs of cost and effect differences and a cost-effectiveness acceptability curve will be made to reflect the probability of Oncokompas being cost-effective given different willingness-to-pay ceilings [43]. Sensitivity analyses will be conducted focusing on uncertainty in the main cost factors.

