#### Medical consumption questionnaire and productivity cost questionnaire

An adapted version of the medical consumption questionnaire (iMCQ) and productivity cost questionnaire (iPCQ) will be used to measure the costs of healthcare (i.e. healthcare use and medication use), the costs for patients and their families (e.g. travelling costs and help received from family or friends), and costs within other sectors (e.g. productivity losses from paid work) in the previous three months. Both questionnaires are developed by the Institute for Medical Technology Assessment of the Erasmus University Rotterdam (iMTA), the Netherlands [36, 37].

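### The cost-utility analysis takes unadjusted arm-mean differences in QALYs and costs although baseline EQ-5D, iMCQ and iPCQ are collected, which gives away precision, mainly for QALYs

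*Protocol article*

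**What the plan says.** All references are to the protocol article.

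- **Economic outcomes** forms the ICUR from two differences. The cost difference is "mean costs in the intervention group minus mean costs in the control group" and the QALY difference is "mean QALYs in the intervention group minus mean QALYs in the control group".
- The same section says how a QALY is built: "QALYs will be calculated by multiplying the EQ-5D utility score by the appropriate time period it accounts for". It does not give the weights for the two utility measurements.
- Its bootstrap is meant "to obtain 95% confidence intervals around the cost and QALY differences". A plane and an acceptability curve follow. The sensitivity analyses named there concern cost factors only.
- **Table 2** (Outcome assessment) marks EQ-5D, iMCQ and iPCQ at t0 and t2 and leaves t1 blank.
- The section on the two cost questionnaires sets the recall window, for instance "costs within other sectors (e.g. productivity losses from paid work) in the previous three months". The t0 costs therefore predate randomization.
- **Statistical analyses** has the only baseline correction: where the arms differ at baseline, "the LMM analyses will be corrected for these differences". Nothing extends this to the cost-utility analysis.

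**The concern.** With utilities at t0 and t2 only, the natural QALY over the three months is the area under a straight line between them. Half of its weight then sits on a utility measured before randomization, which Oncokompas cannot change. A raw comparison of arm means keeps all the between-patient noise in that half. Adjusting for baseline utility removes it, along with the part of the t2 utility that baseline predicts.

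The randomization uses blocks and names no stratification factor, so nothing balances baseline utility or prior costs beyond chance. The horizon is short ("The time horizon will be set at three months follow-up, and therefore neither costs nor effects will be discounted"), so any attainable QALY gain is small compared with that noise. What is at stake is the precision of the QALY difference and, to a lesser degree, of the cost difference, and with them the spread on the plane and in the acceptability curve.

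**Working it through.** **Inputs from the article.** Utilities at t0 and t2; horizon 0.25 year; 1:1 allocation; 68 per arm at baseline and 51 per arm at t2 (Sample size).

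**Inputs assumed, because the article gives none.** Correlation r between the t0 and t2 values, range 0 to 0.7; equal SDs at t0 and t2 unless stated; utility SD 0.25 for the absolute example only.

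**The plan's own figure.** For 0.5 SD, one-tailed alpha 0.05 and power 0.80, the normal approximation gives 2 × (1.645 + 0.842)² / 0.5² = 49.5, so 50 per arm. The exact t calculation gives 50.15, so 51. Then 51 / 0.75 = 68, and 2 × 68 = 136. The sample size reproduces. No precision figure is stated for QALYs or costs.

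**QALYs, complete cases.** With u0 and u2 the utilities at t0 and t2, QALY = 0.25 × (u0 + u2) / 2 = 0.125 (u0 + u2). For n per arm:

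- raw SE = 0.125 × SD × √(2(1 + r)) × √(2/n)
- SE adjusted for u0 = 0.125 × SD × √(1 − r²) × √(2/n)
- raw / adjusted = √(2 / (1 − r))
- share of raw variance due to u0 = (1 + r) / 2

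| r | raw / adjusted SE | share due to baseline |
|---|---|---|
| 0 | 1.41 | 50% |
| 0.3 | 1.69 | 65% |
| 0.5 | 2.00 | 75% |
| 0.7 | 2.58 | 85% |

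Simulation (3,000 trials, 51 per arm) gave adjusted/raw ratios of 0.61, 0.50 and 0.38 at r = 0.3, 0.5 and 0.7. The formula gives 0.59, 0.50 and 0.39.

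**QALYs with the planned dropout.** Patients are randomized after completing t0, so baseline utility is known for 68 per arm and t2 utility for about 51. Suppose that t2 is imputed from baseline utility. The adjusted variance is then proportional to (1 − r²)/51, and the raw variance to (1 + r)²/68 + (1 − r²)/51. Hence

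raw / adjusted = √(1 + 0.75 (1 + r)/(1 − r))

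- r = 0.5: √(1 + 0.75 × 3) = √3.25 = 1.80
- r = 0.6: √(1 + 0.75 × 4) = √4.00 = 2.00
- r = 0.7: √(1 + 0.75 × 5.667) = √5.25 = 2.29

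**Unequal SDs.** If the t2 SD is 1.4 times the t0 SD and r = 0.5 (complete cases), the raw variance is proportional to 1 + 1.96 + 2 × 0.5 × 1.4 = 4.36 and the adjusted variance to 1.96 × 0.75 = 1.47. The factor is √(4.36/1.47) = 1.7, not 2.0.

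**Absolute size (SD 0.25, r = 0.5, 51 complete cases per arm).**

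- 95% half-width: 0.0210 QALY raw, 0.0105 adjusted.
- One SE of chance baseline imbalance: 0.25 × √(2/51) = 0.0495. It shifts the expected raw QALY difference by 0.125 × 1.5 × 0.0495 = 0.0093.
- For scale, a true utility gain of 0.05 at t2 is worth 0.125 × 0.05 = 0.00625 QALY.

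**Costs.** The three-month cost reported at t2 does not contain the baseline cost, so raw / adjusted = 1/√(1 − r²): 1.05, 1.15 and 1.40 at r = 0.3, 0.5 and 0.7. With lognormal costs and those correlations on the log scale, simulated adjusted/raw ratios were 0.99, 0.92 and 0.76, so raw is about 1.01, 1.09 and 1.31 times as wide.

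**The case against.** The strongest reply is that this is a condensed article. The arm-mean wording explains the ICUR formula, adjusted means would fit that formula too, and covariates in an economic model are commonly left to the analysis plan. That carries some weight. But the article spells out the two differences explicitly, goes on to imputation, bootstrap, plane, curve and sensitivity analyses, and limits its baseline correction to another set of models. Read as written, it fixes an unadjusted estimator.

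Several stronger readings are tempting but lack support:

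- **Bias.** Under 1:1 randomization the raw differences are right on average, and the bootstrap already reflects sampling variation from baseline imbalance. The loss is one of precision and of chance imbalance within this one trial.
- **An inflated interval for the ICUR.** None is planned. The intervals are for the cost and QALY differences.
- **A single utility multiplied by three months.** The article does not state this. Its QALY sentence is compatible with the area under the curve; it just omits the weights. If only the t2 utility were used, the gain would be the modest one shown for costs.
- **Much wider cost intervals or a needlessly flat acceptability curve.** The cost gain is small to moderate, and the curve depends on cost variance as well as QALY variance.
- **Adjustment would settle the sign of the QALY difference.** In the example the adjusted half-width of 0.0105 still exceeds the 0.00625 that a 0.05 utility gain is worth.

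**Conclusion.** The point holds as a matter of efficiency. The planned QALY and cost differences ignore baseline values that the trial collects anyway.

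For QALYs by area under the curve with equal SDs, the raw standard error is about 1.4 times the adjusted one even at zero correlation and 2.0 times at 0.5 in complete cases. It is about 1.8 times at 0.5 with the planned dropout and imputation from baseline. The factor falls if utilities spread out by t2. For costs it is about 1.05 to 1.4 at correlation 0.3 to 0.7, and less when costs are skewed.

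All these factors rest on assumed correlations. The QALY factors also rest on t0 entering the QALY, which is the natural reading but is not written down. The point concerns the secondary economic analysis; the primary analysis of patient activation is untouched. The change is worth making because the possible QALY gain is large and the cost is close to nil.

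**What to change.** 1. State that QALYs are the area under the curve between the t0 and t2 utilities.
2. Estimate incremental QALYs by regression on arm and baseline utility, and incremental costs by regression on arm and baseline three-month costs. Do so whatever a baseline significance test shows.
3. Run both regressions inside the planned multiple imputation and the 5000-replicate bootstrap. Take the intervals from the adjusted differences, and draw the plane and acceptability curve from the adjusted pairs.

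The cost is a few lines of analysis text and a little more computing. No new data, patients or visits are needed.
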